### 7.3.4 For men

There are no standard studies on the effect of oxytocin on sperm and reproductive function. It is therefore important to use a double barrier to prevent pregnancy during the study and up to three months after participation in the study (in sub-study 1: pill in combination with -, otherwise mechanical contraceptive methods, e.g. diaphragm, IUD etc. in combination with condoms, see above), because damage to the sperm cannot be ruled out.

### 7.3.5 Measurements in everyday life

The psychological measurements in everyday life (between laboratory appointment 1 and the wound measurement on appointment 3), in which we use a handheld computer to assess mood and current social interactions, do not harbour any medical risk.

The saliva measurements in everyday life (between laboratory appointment 1 and the wound measurement on appointment 3), in which we ask the test subjects to collect saliva samples 6 times a day using saliva vials, do not harbour any medical risk.

### **7.3.6 Stimulus material**

In sub-study 2, the test subjects will see explicit images of couples having sex. These images do not contain any violence. If the subjects feel uncomfortable looking at these images, they can stop the study at any time without giving a reason and without negative consequences. Before the start of the study, we will ask the participants about their experiences and any aversions to sexual images and exclude them from the study if they do not wish to view the images.

### **7.3.7 Eye tracking**

There are no known unpleasant side effects of eye tracking.

### **7.3.8 Psychological questionnaires**

We will use questionnaires to ask the respondents about personality traits and also repeatedly about their mood. We are not aware of any unpleasant side effects of such questioning.

Subjects will be fully informed of all procedures and risks and will sign a consent form before participating in the study. The consent form will include the objectives and risks, as well as the fact that subjects have the right to withdraw from the study at any time. Participation in the study is voluntary and subjects may refuse or withdraw at any time. Under certain circumstances, subjects may also be excluded from the study without their consent if the sponsor ([name]) or the investigator ([name] [name]) feel that it is not in the subjects' best interests to continue with the study or if the procedure is not followed. Subjects are instructed to inform the principal investigators immediately if any adverse events occur in connection with their participation in the study. In such cases, a physician will be on hand immediately to investigate and treat the symptoms and the management of AEs (see above) will take effect.

## **7.4 Efficacy and safety variables**

The efficacy and safety of the investigational product is recorded in both sub-studies using the dependent variables described in each case. Any further effects are queried and documented daily by the test subjects using a checklist, in sub-study 1 via the contact using a handheld computer, in sub-study 2 directly during the contact in the laboratory.

**7.5 (Serious) adverse events, side effects**

**7.5.1 Adverse event (AE)**

An adverse event (AE) is any untoward occurrence that happens to a person participating in the study who has been administered an investigational product and that is not necessarily causally related to this treatment. These can be illnesses, signs of illness, clinically significant laboratory values or symptoms that occur or worsen after the patient has been included in the study.

AEs observed by the investigator or reported by the participant must be recorded in the CRF for the entire duration of the study (from the signing of the informed consent form to the last protocol-specific procedure, regardless of the study medication).

Sufficient information will be obtained from all AEs to allow classification (e.g. as SAE) and to determine the causal relationship to the study medication or study treatment.

Whenever possible, concomitant diseases or conditions that necessitate a therapeutic or diagnostic procedure should be recorded as AEs. Surgery or other invasive procedures that were planned before the start of the study do not have to be recorded as AEs. Such planned procedures are recorded in the CRF by the investigator at the first visit (baseline visit/screening visit).

Pregnancy per se is not an AE. Adverse events that occur in connection with pregnancy must be documented like all other AEs. Pregnancy should be confirmed with an appropriate laboratory test. All pregnancies occurring during the study or up to 30 days after the last receipt of study medication must be reported to the sponsor-investigator within one working day (using a Pregnancy Initial Report Form). If the final visit takes place more than 30 days after the last receipt of study medication, all AEs occurring up to the final visit must be reported. The sponsor-investigator is further required to follow the pregnancy until birth and to document the health status of the newborn with a Pregnancy Follow-Up Report Form.

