#### *Exclusion criteria*

- Indications that the participant is unlikely to comply with the test plan (e.g. unwillingness to cooperate)
- Participation in another clinical trial within the last 4 weeks prior to inclusion
- Skin disease
- Accident with neurological sequelae
- Allergies or a history of known hypersensitivity to one of the drugs used or their ingredients, or to drugs with a similar chemical structure
- UV-B irradiation in the last 3 months before the examination
- Taking medication
- Drug use, addiction or other illnesses that do not allow the person concerned to the nature, scope and possible consequences of the clinical trial
- Overweight or underweight
- Daily alcohol consumption ( $> 60g$  alcohol, equivalent to approx. 7.5 dl wine or 2 litres beer per day)
- No participation of the Investigator or his/her family members, employees or other dependent persons
- Women: Pregnancy (for instructions on the double barrier to prevent pregnancy, see subject information) or intention to become pregnant during the course of the study

- Women: Breastfeeding

These criteria are queried with the interested participants in a telephone interview. No personal details are recorded during this telephone interview, so that no personal data can be linked to the inclusion or exclusion criteria before the consent form is signed. An appointment for the study is arranged with interested and suitable test subjects, at which the inclusion and exclusion criteria are discussed again and the test subjects sign the declaration of consent.

For this study, it is essential that certain things are controlled, as these activities or factors influence the measured values and may make them unusable. For this reason, the test subjects were asked to follow the instructions bellow:

- Do not drink coffee or other caffeinated drinks (cola, energy drinks, etc.), black tea or alcohol on the afternoon of the first laboratory appointment (approx. from 3 pm),
- Do not engage in excessive sport on the day of the examination,
- Do not smoke immediately before the 1st laboratory appointment,
- No physical exertion (cycling etc.) immediately before the 1st laboratory appointment,
- Do not eat anything heavy immediately before the 1st lab appointment.

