**Oxytocin/placebo administration + interaction**

After application of the wound, cytokine measurement 1 is performed and TEWL is measured. The test subjects are then given intranasal double-blind placebo or oxytocin (24IU, 3 sprays per nostril; both partners receive either placebo or oxytocin). The positive couple interaction is then explained and practiced. During this exercise, the couples are recorded on video. The first session lasts approximately 2.5 hours (see Figure 1).

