#### 6.4.1 Study sample and power analyses

In sub-study 2, 88 people (44 women, 44 men) will be examined who will receive either oxytocin nasal spray or placebo nasal spray. The probability of allocation to one of the two groups is 50%. The participating women will be analysed twice during two different cycle phases. Power analyses suggest a sample size of  $N=82$  for sub-study 2 with regard to the main outcome variable preference (gaze duration) (effect  $d=.60$ ; power = .85,  $\alpha = .05$ ). With an assumed effect  $f = .50$ ,  $\alpha = .05$  and an  $N = 20$ , a power of  $\beta = .85$  can be assumed for the repeated measurement of the female participants. The total  $N$  is therefore set to  $N=88$  in order to compensate for any dropouts.

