1127 **7.9 Follow-up of (serious) adverse events**

1128 The health status of participating persons who discontinue the study (regularly or premature-  
1129 ly) due to

- 1130 • reported, persistent SAE, or
- 1131 • persistent adverse event, e.g. laboratory values or alarming vital signs,

1132 is examined at a follow-up visit. This visit takes place up to 30 days after the end of the study  
1133 treatment. The follow-up information is recorded on the corresponding AE page of the CRF.  
1134 The corresponding medical file must be available for inspection upon request.

1135 Efforts to find lost to follow-up patients must be made and documented. In the case of minor  
1136 AEs, telephone calls may be sufficient.

1137 New SAEs or pregnancies must be reported using the appropriate forms and entered in the  
1138 CRF within 30 days of the last dose of study medication. The reporting obligation is extended  
1139 until the final visit if this takes place later than 30 days after the last treatment with the study  
1140 medication.

1141 Follow-up visits may also be necessary at the discretion of the investigator, even if the partic-  
1142 ipant does not have an AE at the end of the study. The information of such visits only needs to  
1143 be documented in the medical record, not in the CRF.

1144 **8 Data Quality Assurance**

1145 Monitoring and quality assurance audits are carried out as part of the clinical trial.

1146 **8.1 Monitoring**

1147 Regular monitoring during the study checks the collection of data, ensures compliance with  
1148 the protocol, ensures the accuracy of the data and enables errors to be detected at an early  
1149 stage. The sponsor is responsible for organising professional, independent monitoring.

1150 The documents relating to the study, CRFs, study-relevant original patient files, laboratory  
1151 and medical test results must be available for inspection by the monitor. The monitor reviews  
1152 CRFs and patient consent forms. The accuracy of the data is verified by reviewing the above  
1153 documents.

1154 The Centre for Clinical Research (CTC) of the University Hospital Zurich will ensure moni-  
1155 toring at the trial site. The monitoring will be performed according to ZKF/CTC SOPs. The  
1156 type and frequency of monitoring will be defined in the separate monitoring plan.

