## 1232 **9 Insurance**

1233 The insurance is covered by the liability insurance for the University of Zurich, which was  
1234 taken out specifically for this study. This covers all damages in connection with the study.  
1235 Study participants must strictly adhere to the instructions of the study personnel. Furthermore,  
1236 they may not undergo any other medical treatment during the clinical trial without the consent  
1237 of the investigator (with the exception of emergencies). They must inform the investigator

1238 immediately of any emergency treatment. If health problems or other damage occur during or  
1239 after participation in the study, the investigator must be informed. A copy of the insurance  
1240 certificate will be filed in the trial centre folder.

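### Pregnancy reporting stops 30 days after the last dose, although the protocol's precaution for men runs up to three months after participation

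*Protocol*

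**What the plan says.** **The precaution for men.** Section 7.3.4 notes that standard studies of oxytocin's effect on sperm and reproductive function are lacking. It therefore calls it important to "use a double barrier to prevent pregnancy during the study and up to three months after participation in the study", since damage to the sperm cannot be excluded.

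**The reporting duty.** Section 7.5.1 states: "All pregnancies occurring during the study or up to 30 days after the last receipt of study medication must be reported". For pregnancies caught by this rule, the sponsor-investigator must follow the pregnancy to birth and record the newborn's health on a dedicated form. Section 7.9 repeats the limit: new SAEs and pregnancies are to be reported and entered in the "CRF within 30 days of the last dose of study medication". It prolongs the duty to the final visit only when that visit falls more than 30 days after the last treatment.

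**Other follow-up.** Section 7.9 defines a follow-up visit for persistent adverse events, which takes place no later than 30 days after treatment. It also allows later visits at the investigator's discretion. For participants without an adverse event, the information from these need only "be documented in the medical record, not in the CRF".

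**The concern.** The protocol sets two periods for the same question and does not align them. In 7.3.4 it treats conception through a dosed man as a possible risk for up to three months. In 7.5.1 and 7.9 it stops asking about pregnancies after 30 days. Pregnancy reporting exists for the cases in which contraception fails or is not used, so it should last as long as the precaution it backs up.

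At stake is a pregnancy conceived through a dosed man after day 30 but inside the three-month window. Nothing obliges anyone to report it, and the follow-up to birth required by 7.5.1 does not start. Any information on the outcome would reach the sponsor only by chance.

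**Working it through.** No sample size, power or error rate is involved. The check compares the two windows with the visit schedule.

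**Inputs**
- Male precaution: up to three months after participation (7.3.4).
- Pregnancy reporting: 30 days after the last dose (7.5.1, 7.9).
- Sub-study 1: dosing on six days, so the last dose is on day 6 (synopsis; 5.6.1). The last wound measurement is 7 days after application (5.7.2), while the visit plan puts the last visit on day 6.
- Sub-study 2: "The participating women will be analysed twice during two different cycle phases" (6.4.1). No repeat is described for men, so a man's one scheduled visit is his dosing visit.
- Men: 100 in sub-study 1 (100 heterosexual couples) and 44 in sub-study 2. Allocation to oxytocin has probability 50% in each (5.4, 6.4.1).

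**Step 1: length of the precaution.** Three calendar months starting within the timetable (02/2011 to 02/2013) last 89 to 92 days.

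**Step 2: does the extension clause apply?**
- Sub-study 1: with application on day 1, the last measurement is on day 1 + 7 = day 8. That is 8 − 6 = 2 days after the last dose, or 0 days if the visit is on day 6. Both are below 30.
- Sub-study 2, men: 0 days after the dose, also below 30.

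No scheduled visit triggers the extension.

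**Step 3: uncovered time = (days from last dose to end of participation) + (three months) − 30**
- Sub-study 2, and sub-study 1 with a day-6 visit: 0 + 89 − 30 = 59 to 0 + 92 − 30 = 62 days.
- Sub-study 1 with a day-8 visit: 2 + 89 − 30 = 61 to 2 + 92 − 30 = 64 days.
- Overall: 59 to 64 days.

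**Step 4: men to whom the gap applies.** 100 + 44 = 144. On oxytocin: 0.5 × 100 + 0.5 × 44 = 50 + 22 = 72 expected.

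**Step 5: could *during the study* mean the whole trial calendar?** Section 7.5.1 sets the period for recording adverse events person by person, from consent to the last protocol-specific procedure. A calendar-wide reading would also leave the 30-day limit with little to do. The individual reading is the natural one.

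**The case against.** **The two periods need not match.** One is preventive advice and the other a duty to collect data, and each can be followed without breaching the other. That is true, so this is not a formal contradiction. But the longer window is the protocol's own choice, on stated grounds, and the reporting rule does not serve it.

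**Other routes exist.** Section 9 says that if health problems or other damage arise during or "after participation in the study, the investigator must be informed", with no end date. Section 7.5.3 lists congenital malformation among the seriousness criteria, and 7.9 allows discretionary visits. These may bring a harmful outcome to light. They do not oblige anyone to report an uncomplicated pregnancy, so they do not start follow-up to birth.

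**The basis is thin.** Men receive one dose in sub-study 2 and six days of dosing in sub-study 1, half of them on placebo, and 7.3.4 cites absent studies rather than an observed effect. This stands, and it sets the weight.

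**Stronger readings a reader might infer, which the document does not support**
- *That men are strictly required to use contraception.* Section 7.3.4 calls it important and says up to three months; it sets no absolute rule.
- *That partners' pregnancies are excluded.* The wording in 7.5.1 covers all pregnancies and excludes nobody. In sub-study 1 the woman is a participant herself ("both partners receive either placebo or oxytocin"), so the question does not arise. In sub-study 2 the partner need not be a participant, and naming her is only a clarification, for 44 men.
- *That men should be screened for plans to conceive.* A reporting window can be corrected without a new exclusion. Such a criterion would cost enrolees, and it may overlap with the subject information, to which the criteria refer for contraception and which is not available here. For the same reason, nothing is claimed about what men are told.

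**Conclusion.** The point holds as a low-weight gap in safety data capture. About two months of the protocol's own precautionary window for men, 59 to 64 days at full length, carry no duty to report a pregnancy or follow it to birth.

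The figure assumes that the three months are used in full, that *during the study* is read per participant, and that no discretionary visit takes place after day 30. It is calendar time, not a share of risk. The document gives no conception rate, so no number of missed pregnancies can be stated. A reader might infer that oxytocin is suspected of harming offspring; 7.3.4 reports only a lack of studies. Randomisation, blinding, sample size and every efficacy analysis are untouched.

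**What to change.** In 7.5.1 and 7.9, extend pregnancy reporting to conceptions up to three months after the end of participation where the father is a dosed participant. Apply it in both arms so that blinding is kept. State that in sub-study 2 this includes partners of male participants, with follow-up to birth subject to the partner's agreement. Ask men at their last visit to notify the site, and use the existing Pregnancy Initial Report and Follow-Up Report Forms. Leave the eligibility criteria as they are.

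The cost is wording in two sections, one request at the last visit, slight extra follow-up, and the work of obtaining consent from partners who are not in the trial. It is a cheap improvement.

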**7.5.2 Adverse drug reaction (ADR)**

An adverse reaction (AR) is any adverse and unintended reaction to an investigational medicinal product, regardless of its dosage. Classification as a reaction is made if a connection between the event and the investigational medicinal product is at least considered possible.

1018 An Unexpected Adverse Reaction (UAR) is an adverse reaction that is not consistent in type  
1019 or severity with the available information on the investigational medicinal product.

### 1020 **7.5.3 Serious Adverse Event (SAE)**

1021 An SAE or Serious Adverse Reaction (SAR) is any adverse event or side effect that

- 1022 • leads to death or
- 1023 • is life-threatening or
- 1024 • leads to permanent or severe disability or invalidity, or
- 1025 • requires inpatient treatment or its extension, or
- 1026 • leads to congenital malformations or birth defects or
- 1027 • is medically significant for other reasons (event requiring medical intervention to pre-  
1028 vent an outcome considered serious).

### 1029 **7.5.4 Suspected Serious Unexpected Adverse Reaction (SUSAR)**

1030 A suspected case of an Unexpected Serious Adverse Reaction is referred to as a Suspected  
1031 Unexpected Serious Adverse Reaction (SUSAR). A serious adverse reaction is unexpected if  
1032 it is not listed in the Information for healthcare professionals/ IB.

## 1033 **7.6 Documentation of (S)AEs**

1034 The investigator will ask the participant at each visit and via handheld computer how they are  
1035 feeling. It is the responsibility of the investigator to document all adverse events, including  
1036 intercurrent illnesses, in the CRF. The time from which AEs are documented is the signature  
1037 of the informed consent form.

1038 If an adverse event occurs, the affected person must be observed in any case, regardless of the  
1039 causal relationship between the event and the investigational product, until the symptoms  
1040 have subsided or pathological laboratory values have returned to the initial values, or until, in  
1041 the opinion of the principal investigator, no further findings are to be expected. If the adverse  
1042 event results in a persistent sequela, this must be classified as an SAE and documented ac-  
1043 cordingly at the end of the study. All findings and results must be documented on the corre-  
1044 sponding page for Adverse Events in the CRF.

1045 The following information is required:

- 1046 • Type of adverse event (sign, symptom or disease, diagnosis if possible),
- 1047 • Assessment of (worsening of existing) concomitant diseases as an adverse event,
- 1048 • Differentiation (serious/not serious)
- 1049 • Start and end of occurrence,
- 1050 • Intensity (mild = easily tolerated, moderate = affects daily activities, severe = daily ac-
- 1051 tivities/work not possible; CTC criteria only recommended in oncological studies),
- 1052 • Causality to the investigational medicinal product,
- 1053 • Measures relating to the investigational medicinal product or actions to restore or im-
- 1054 prove the well-being of the person concerned,
- 1055 • Outcome of the event.

1056 The following points must be strictly adhered to when documenting the SAEs:

- 1057 • the SAE must be documented on the corresponding AE page in the CRF and on the
- 1058 SAE form,
- 1059 • Each SAE must be reported as completely as possible. (in the event of death, an autop-
- 1060 sy should be performed if possible and the report made available to the Principal In-
- 1061 vestigator),
- 1062 • the person responsible for monitoring must check the data at the test centre for com-
- 1063 pleteness and ensure that the information in the SAE report matches the information in
- 1064 the database and other data sources.

1065 Cases of overdose, misuse, application errors, etc. should be documented, even without an AE  
1066 occurring.

### 1067 ***7.7 Assessment of (Serious) Adverse Events***

1068 The Investigator will review documented AEs or abnormal test results as soon as possible to  
1069 determine if

- 1070 • the abnormal test result is to be classified as an AE
- 1071 • there is a possibility that the study medication or the study treatment triggered the AE,
- 1072 and
- 1073 • whether the criteria for an SAE are met.

1074 The causal relationship of the (S)AE with the investigational product is determined by the  
1075 investigator according to the following definitions:

1076 **Unlikely relation:** the temporal relationship with the administration of the study medication  
1077 makes a causal relationship unlikely and other drugs, chemicals or underlying diseases offer a  
1078 plausible explanation.

1079 **Possible relation:** the temporal relationship between administration of the study medication  
1080 and occurrence of the (S)AE is given, but other drugs, chemicals or underlying diseases offer  
1081 a plausible explanation, or information from discontinuation of the study medication is miss-  
1082 ing or unclear

1083 **Likely relation:** the temporal relationship between the administration of the study medication  
1084 and the occurrence of the (S)AE is given, and other drugs, chemicals or underlying diseases  
1085 do not provide a credible explanation, and the discontinuation of the study medication  
1086 (dechallenge) is followed by an appropriate response. Information about a rechallenge is not  
1087 necessary to fulfil this definition.

1088 **Certain relation:** the temporal relationship between the administration of the study medica-  
1089 tion and the occurrence of the (S)AE is given, and other drugs, chemicals or underlying dis-  
1090 eases offer no plausible explanation, and discontinuation of the study medication (dechal-  
1091 lenge) is followed by a clinically plausible reaction. The event is pharmacologically **and** phe-  
1092 nomenologically definite, demonstrated by rechallenge if necessary.

